## Abstract

**Background:**

The most important action in the resuscitation of a newborn in the delivery room is to establish effective assisted ventilation. The face mask and endotracheal tube are the devices used to achieve this goal. Laryngeal mask airways that fit over the laryngeal inlet have been shown to be effective for ventilating newborns at birth and should be considered as an alternative to facemask ventilation or endotracheal intubation among newborns weighing >2,000 g or delivered ≥34 weeks’ gestation. A recent systematic review and meta-analysis of supraglottic airways in neonatal resuscitation reported the results of four randomized controlled trials (RCTs) stating that fewer infants in the group using laryngeal mask airways required endotracheal intubation (1.5%) compared to the group using face masks (12.0%). However, there were methodological concerns over all the RCTs including the fact that the majority of the operators in the trials were anesthesiologists.

Our hypothesis is based on the assumption that ventilating newborns needing positive pressure ventilation with a laryngeal mask airway will be more effective than ventilating with a face mask in a setting where neonatal resuscitation is performed by midwives, nurses, and pediatricians. The primary aim of this study will be to assess the effectiveness of the laryngeal mask airway over the face mask in preventing the need for endotracheal intubation.

**Methods/design:**

This will be an open, prospective, randomized, single center, clinical trial. In this study, 142 newborns weighing >1,500 g or delivered ≥34 weeks gestation needing positive pressure ventilation at birth will be randomized to be ventilated with a laryngeal mask airway (LMA Supreme^TM^, LMA Company, UK - intervention group) or with a face mask (control group). Primary outcome: Proportion of newborns needing endotracheal intubation. Secondary outcomes: Apgar score at 5 minutes, time to first breath, onset of the first cry, duration of resuscitation, death or moderate to severe hypoxic-ischemic encephalopathy within 7 days of life.

**Trial registration:**

ClinicalTrials.gov identifier: NCT01963936 (October 11, 2013).

## Background

The ability to maintain a patent airway and provide effective positive pressure ventilation (PPV) is the main objective of neonatal resuscitation [1,2]. This is currently achieved with the use of a face mask (FM) or an endotracheal tube (ETT). Both these devices have major limitations from a strictly anatomical point of view and require adequate operator skills. In certain situations, both FM ventilation and ETT intubation may prove difficult to establish an upper airway [3,4].

In 1981, Archie Brain designed the laryngeal mask airway (LMA) with the aim of producing an airway device that would be more practical than the FM and less invasive than the ETT [5].

In adults, the LMA is routinely used during anesthesiology procedures.

The potential advantages of the LMA over the FM include an easier insertion technique, less manipulation of the patient’s head, neck, and jaw, a better airtight seal after positioning, and more effective PPV [6]. Ease of positioning and reduced invasiveness are the reported advantages of the LMA when compared to the tracheal tube [6].

A recent study including 11,910 anesthesia pediatric cases showed that only 102 cases (0.86%) experienced LMA failure. Common presenting features of LMA failures included leak (25%), obstruction (48%), and patient intolerance such as intractable coughing/bucking (11%) [7].

In the setting of the neonatal resuscitation, previous observational studies showed that, when used by teams with expertise (that is, anesthesiologists), the LMA provided effective PPV in most of the treated patients (range 95 to 99%) [8-10]. A 2005 Cochrane review concluded that there was no evidence to evaluate the safety or efficacy for the use of LMA versus FM ventilation in the resuscitation of newborn infants [11]. It suggested that a well-designed randomized controlled trial (RCT) comparing these two airway adjuncts was warranted [11]. In 2013, a systematic review and meta-analysis of supraglottic airways in neonatal resuscitation reported the results of four RCTs, stating that fewer infants in the LMA group required endotracheal intubation (1.5%) compared to the FM group (12.0%) [12]. There were however, methodological concerns over all the RCTs including the fact that the majority of the operators in the trials were anesthesiologists (who are less likely in most clinical settings to be present at neonatal resuscitation).

The LMA is used more often by anesthesiologists rather than pediatricians, nurses, and midwives. It is thus essential to demonstrate its effectiveness by those who will be more commonly involved in neonatal resuscitation in most clinical settings. Furthermore, it is important to thoroughly record any side effects, as in a case series of a comparison of LMA over FM in infants in the operating theatre, significantly more side effects were reported using the LMA over the FM [13,14].

Although previous studies showed that the LMA was effective also in preterm infants weighing less than 2,000 g [9,10], the last version of the International Guidelines for Neonatal Resuscitation state that “a LMA should be considered during resuscitation if FM ventilation is unsuccessful and tracheal intubation is unsuccessful or not feasible. The LMA may be considered as an alternative to a FM for PPV among newborns weighing >2,000 g or delivered ≥34 weeks’ gestation” [1,2].

Despite this recommendation, it has not yet been shown in a well-conducted RCT whether or not LMA is more effective than FM in resuscitation of newborn infants.

## Methods/design

### Aim

The primary aim of this study will be to assess the effectiveness of LMA over FM ventilation in preventing the need for endotracheal intubation at birth.

### Study design

This is a single center, prospective, unblinded, randomized clinical trial of LMA ventilation versus FM ventilation in infants weighing >1,500 g or delivered ≥34 weeks’ gestation.

### Inclusion criteria

Inborn infants satisfying the following inclusion criteria will be eligible to participate in the study:

1. gestational age ≥34 weeks (and)

2. expected birth weight >1,500 g [9,10] (and)

3. need for PPV at birth; the need for PPV will be determined by the presence of apnoea or gasping, or heart rate <100 beats per minute (bpm) after initial resuscitation measures (providing warmth, positioning, clearing the airway, drying and stimulation) over the first 30 seconds [1,2] (and)

4. parental consent; a written informed consent will be obtained by a member of the neonatal team involved in the study from a parent or guardian before delivery.

### Exclusion criteria

1. Lethal anomalies.

2. Hydrops.

3. Major malformations of the respiratory system.

4. Congenital heart disease.

5. Stillbirths; a stillbirth will be diagnosed when a heart rate is never established.

### Primary outcome measure

The primary outcome of this study will be the proportion of newborns needing endotracheal intubation.

### Secondary outcome measures

1. Apgar score at 5 minutes.

2. Time to first breath, defined as the first respiratory effort.

3. Time to first cry, defined as the first audible cry spontaneously emitted by the infant.

4. Death or moderate to severe hypoxic-ischemic encephalopathy (HIE) within 7 days of life, according to a modification of Sarnat and Sarnat [15,16]. According to this classification, HIE grade I (mild) includes irritability, hyperalertness, mild hypotonia, and poor sucking; grade II (moderate) includes lethargy, seizures, marked abnormalities of tone, and requirement of tube feeding; grade III (severe) includes coma, prolonged seizures, severe hypotonia, and failure to maintain spontaneous respiration.

5. Complications secondary to the procedure.

6. Admission to NICU/normal nursery.

### Other collected data

The following data will be collected during resuscitation: (1) Apgar score at 1 min after birth; (2) LMA insertion time, the rate of successful insertion at the first attempt, and the number of attempts required to insert the LMA successfully; (3) adverse effects during resuscitation.

### Generalizability

The findings of this study will be important for other units/settings in high as well low resource countries where neonatal resuscitation is more often performed by pediatricians, midwives, or nurses. Based on the results of the present study, we could speculate whether a short-term educational program on the LMA use will be effective in the clinical practice; furthermore, we will be able to understand whether personnel involved in neonatal resuscitation should be trained to start resuscitation with an FM or with an LMA. Finally, potential complications and side effects due to the LMA will be strictly monitored and collected.

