### Blinding

Due to the characteristics of the intervention, neither caregivers nor outcome assessors will be masked to treatment allocation. To minimize bias, strict criteria and definitions will be maintained during the trial.

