### Data collection

Data will be recorded from clinical records and from a data sheet designed for this study, where all the data obtained during resuscitation procedures will be collected by an observer not involved in the resuscitation maneuvers. Registered clinical information will be: eligibility, antenatal history, randomization, and all data above listed in the ‘Primary outcome measure’, ‘Secondary outcome measures’ and ‘Other collected data’ sections. Further information will be collected on expected serious adverse events (SAEs).

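### Secondary outcome 5 counts complications by attributed cause in an open trial, which risks unequal ascertainment between the arms

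*Protocol article*

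**What the plan says.** All references are to the Protocol article.

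- **Secondary outcome measures**, item 5: "Complications secondary to the procedure". The item gives no list of events and does not say who makes the attribution.
- **Blinding**: "neither caregivers nor outcome assessors will be masked to treatment allocation". The stated safeguard is: "To minimize bias, strict criteria and definitions will be maintained during the trial".
- **Generalizability**, last sentence: "potential complications and side effects due to the LMA will be strictly monitored and collected".
- **Other collected data**, item 3: "adverse effects during resuscitation", with no condition on arm or cause.
- **Data collection**: resuscitation data go on a study data sheet and are "collected by an observer not involved in the resuscitation maneuvers". Information on expected serious adverse events is also collected.
- **Safety**: frequency, severity and causality of serious adverse events are assessed in both arms, including unexpected events. Suspected causality limits only which of them go to the ethics committee.
- **Randomization**: the assigned procedure means positive pressure ventilation with either device, so outcome 5 applies to both arms.
- **Statistical analysis**: categorical data are compared with Fisher's test, with significance at P below 0.05.

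**The concern.** An outcome that requires a causal judgement is only as even-handed as the person judging, and here that person may know the device. An event after insertion of a laryngeal mask can readily be linked to it, while the same event after face-mask ventilation may be put down to the infant's condition. The judgement could also err the other way. The wording under Generalizability does not help, because it directs strict attention to one device.

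The Generalizability section says the trial should inform whether staff start resuscitation with a face mask or a laryngeal mask. Complications bear on that choice. If ascertainment differs by arm, the comparison of outcome 5 could show an excess that is not there or hide one that is. A larger sample would not cure this, and no analysis can recover events that were never counted.

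**Working it through.** **Step 1. Which harm records carry which limit?**

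| Record | Section | Limited to one arm? | Limited by cause? | Serious only? | Period |
|---|---|---|---|---|---|
| Outcome 5 | Secondary outcome measures | No | Yes | No | Not stated |
| Adverse effects | Other collected data | No | No | No | During resuscitation |
| Serious adverse events | Data collection; Safety | No | No (only the report to the ethics committee is) | Yes | Followed until resolved, chronic or stable |
| Strict-monitoring sentence | Generalizability | Names the laryngeal mask only | Yes | No | Not stated; not a collection rule |

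**Step 2. What falls outside the unfiltered records?** An event during resuscitation is caught by row 2 and a serious event by row 3, in either arm and whatever the cause. A non-serious event seen after resuscitation has no stated route except outcome 5, where it must first be attributed to the procedure. Events during resuscitation are recorded without a filter, but under other collected data. The declared outcome still applies the filter to them.

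**Step 3. Does the stated safeguard reach outcome 5?** The Blinding section relies on strict definitions. Among the clinical outcomes, time to first breath, time to first cry and encephalopathy are given definitions in the outcome list; complications are not. The observer is outside the resuscitation maneuvers but is not said to be masked.

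**Step 4. How much could it matter?** The plan gives no complication rate, so there is no figure to reproduce. What follows is illustration on assumed rates.

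Observed rate = true rate × share of events counted. With a true rate of 15% in both arms, 90% counted under the laryngeal mask and 45% under the face mask:

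- laryngeal mask: 0.15 × 0.90 = 0.135, or 13.5%
- face mask: 0.15 × 0.45 = 0.0675, or 6.8%
- ratio: 0.135 / 0.0675 = 0.90 / 0.45 = 2.0

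The ratio of 2.0 only restates the assumed counting shares, so a range is more informative. Take 142 / 2 = 71 infants per arm, no dropouts, equal true rates, all laryngeal-mask events counted, and a two-sided Fisher test at P below 0.05. (The Statistical analysis section does not state sidedness; two-sided is assumed here.) The chance of a false significant result is the sum, over all pairs of counts that Fisher's test calls significant, of the product of the two binomial probabilities.

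| True rate, both arms | Face-mask share counted | Expected observed rates (laryngeal mask v face mask) | Chance of P < 0.05 |
|---|---|---|---|
| 10% | 100% | 10% v 10% | 2.6% |
| 10% | 75% | 10% v 7.5% | 4.3% |
| 10% | 50% | 10% v 5% | 11.7% |
| 20% | 100% | 20% v 20% | 3.2% |
| 20% | 75% | 20% v 15% | 8.6% |
| 20% | 50% | 20% v 10% | 31.0% |
| 30% | 100% | 30% v 30% | 3.2% |
| 30% | 75% | 30% v 22.5% | 12.8% |
| 30% | 50% | 30% v 15% | 50.1% |

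With equal arms and a two-sided test, the figures are the same if laryngeal-mask events are the ones under-counted.

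**The case against.** The case against is substantial and removes the stronger readings.

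- **A reader might infer that harms in general count only when attributed.** They do not. Adverse effects during resuscitation and serious adverse events are collected without that condition. This stands, and it confines the point to outcome 5.
- **A reader might infer that face-mask harms are monitored less.** The sentence quoted from Generalizability states an intention about the newer device. It is not a collection rule and says nothing about the face mask. The operative sections do not differ by arm. This stands.
- **A reader might infer that unmasked caregivers make the attribution.** No section names who does. All that is stated is that neither caregivers nor assessors are masked. This stands as a limit on what can be claimed, but it offers no protection either.
- **A reader might take the Background as evidence that staff expect more harm from the laryngeal mask.** It says "significantly more side effects were reported using the LMA over the FM", but of a case series in the operating theatre, given as a reason to record side effects carefully. It is no evidence of what the staff in this trial expect.
- **The event list may sit on the data sheet or in a full protocol, neither of which is shown.** It may, and its absence from an article is no fault. The point rests instead on how the outcome is worded: filtered by cause. A list on the data sheet would not remove that filter unless the outcome were redefined.

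Masking is not feasible with these devices and its absence is disclosed. That is a reason to choose an outcome definition that depends less on judgement.

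**Conclusion.** The point holds in limited form. One secondary outcome is defined by causal attribution in an open trial, and the only explicit promise of strict monitoring of complications names one device. Together these create a risk of differential ascertainment in outcome 5, chiefly for non-serious events noticed after resuscitation.

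The documents do not show that unequal ascertainment will occur, in which direction, or by how much, so it would be wrong to say that the comparison is biased. The figures above rest wholly on assumed event rates and counting shares. They show that a moderate imbalance (75% counted in one arm) has a small to moderate effect, and that a severe one (50%) could dominate the comparison when events are common. The primary outcome, need for endotracheal intubation, is not touched by this point. It is a cheap improvement, not a threat to the trial's main conclusion.

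**What to change.** 1. In **Secondary outcome measures**, redefine item 5 as the occurrence of any event on one prespecified list, recorded for every infant in both arms over the same stated period, regardless of suspected cause. The investigators should choose the events and the period.
2. Keep causality judgements for the assessment and reporting of serious adverse events under **Safety**.
3. In **Generalizability**, extend the strict-monitoring sentence to both arms, in line with Other collected data, Data collection and Safety.

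**Cost.** One checklist on the existing data sheet, completed by the existing observer. Some unrelated events will be counted in both arms, which adds a little noise. The list reduces the dependence on judgement but does not remove it, since the recorder is still unmasked. The Trial status section says recruitment is under way, so the change should be dated and made without sight of complications by arm. For infants already enrolled, the new definition can be applied only as far as the events were recorded at the time.

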### Sample size

It is estimated that 5% of newborns receive resuscitation with PPV [1,2]. Therefore, in C hospital, Hanoi, Vietnam with more than 20,000 deliveries per year, approximately 1,000 patients will require resuscitation. Of these, about 90% (900 neonates) are newborns weighing >1,500 g or delivered ≥34 weeks gestation.

The sample size was based on a previous study in which the success rate of LMA and FM were 99% and 84%, respectively [17]. To obtain a 90% power at a 0.05 level of significance (one-sided), at least 58 subjects per group need to be enrolled. The number of patients was increased by 20% for each group considering the possibility of dropouts, leading to a final sample of 142 subjects.

### Recruitment

Written and oral information will, whenever possible, be offered to parents prior to the birth of their child if the infant is likely to be eligible. Informed written consent will be signed by a parent or guardian. A senior investigator will be available at all times to discuss concerns raised by parents or clinicians during the course of the trial.

### Randomization

Eligible infants will be assigned to the LMA or the FM group in a 1:1 ratio according to a computer-generated, randomized sequence. The randomized allocation will be concealed in double-enclosed, opaque, sealed, and sequentially numbered envelopes prepared at the University Hospital of Padua.

In the delivery room or operating room, the next sequential randomization envelope will be opened only when the infant will be considered to be eligible by the attending operator. The assigned procedure (PPV with LMA or FM) will then be performed. Multiple births will be separately randomized.

### Blinding

Due to the characteristics of the intervention, neither caregivers nor outcome assessors will be masked to treatment allocation. To minimize bias, strict criteria and definitions will be maintained during the trial.

In this study, the last model of size 1 LMA Supreme (LMA Supreme™, LMA Company, UK) will be used [18]. Previous studies conducted in adult patients showed the efficacy and the safety of the LMA Supreme [19,20]. The LMA Supreme is superior to the LMA Classic™ with regard to insertion time and oropharyngeal seal pressure [21]; a further advantage consists in the gastric access.

A previous neonatal manikin study confirmed these findings, including a higher level of satisfaction expressed by users [22].

### Data collection

Data will be recorded from clinical records and from a data sheet designed for this study, where all the data obtained during resuscitation procedures will be collected by an observer not involved in the resuscitation maneuvers. Registered clinical information will be: eligibility, antenatal history, randomization, and all data above listed in the ‘Primary outcome measure’, ‘Secondary outcome measures’ and ‘Other collected data’ sections. Further information will be collected on expected serious adverse events (SAEs).

### Statistical analysis

Categorical data will be expressed as number and percentage and compared using Fisher’s test. Continuous data will be expressed as mean and standard deviation or median and interquartile range. The normality assumption of continuous variables will be evaluated using Shapiro-Wilk test. Continuous data will be compared using Student’s *t*-test or the Mann-Whitney non-parametric test. Correlation between continuous data will be evaluated using the Pearson correlation coefficient or the Spearman correlation coefficient. A *P*-value less than 0.05 will be considered significant. Statistical analysis will be performed using the R 2.12 language [23].

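### Fisher's test on the primary outcome is valid but uses only about 2–3% of the 5% error rate; Boschloo's exact test would recover 1.6 to 13.0 points of power from the same infants

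*Protocol article*

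**What the plan says.** In the protocol article, the section Primary outcome measure defines a binary endpoint: "The primary outcome of this study will be the proportion of newborns needing endotracheal intubation". The Statistical analysis section names one test for every variable of that kind: "Categorical data will be expressed as number and percentage and compared using" Fisher's test. It adds: "A *P*-value less than 0.05 will be considered significant". It does not say whether that threshold is one- or two-sided.

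The Sample size section rests on an earlier study in which "the success rate of LMA and FM were 99% and 84%, respectively". It then states: "To obtain a 90% power at a 0.05 level of significance (one-sided), at least 58 subjects per group need to be enrolled". A 20% allowance for dropout brings the total to 142, or 71 per group at 1:1 allocation. The Background section gives a second, less favourable pair of intubation rates from a meta-analysis: 1.5% with the laryngeal mask and 12.0% with the face mask.

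**The concern.** Fisher's test conditions on the total number of events. With few intubations, only a handful of tables are possible for each total, so the attainable P-values are coarse and the test usually stops well short of the nominal 5%. The unspent error rate is unspent power. The z formula behind the 58 per group makes no allowance for this.

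The protocol gives a reason to care. Its planning rates come from a single study, which the Discussion describes as quasi-randomized. The Background notes that most operators in the earlier trials were anesthesiologists, whereas this trial tests other staff. If the true contrast is nearer to 1.5% v 12% than to 1% v 16%, power is no longer comfortable and the choice of exact test matters more.

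**Working it through.** **Inputs.** Planning success rates are 99% and 84% (Sample size). Taking failure as intubation, which is an assumption, this is 1% v 16%. The alternative is 1.5% v 12% (Background). The group sizes are 58 (Sample size) and 142/2 = 71. The level is 0.05; both one- and two-sided tests are shown, because the design is one-sided and the analysis section is silent.

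**Step 1: reproduce the 58.** Pooled z formula without continuity correction, with p̄ = (0.84 + 0.99)/2 = 0.915:

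n = [z₀.₉₅·√(2p̄(1−p̄)) + z₀.₉₀·√(p₁(1−p₁) + p₂(1−p₂))]² / (p₁−p₂)²

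= [1.645 × √0.15555 + 1.282 × √(0.1344 + 0.0099)]² / 0.15² = 57.3, so 58.

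This matches exactly. The same one-sided formula with a continuity correction, which approximates Fisher's test, gives 71. The stated size therefore comes from a formula that does not reflect the stated test.

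**Step 2: Fisher's actual error rate.** With b(·; n, p) the binomial probability and R the set of tables with Fisher P < 0.05, size(p) = Σ over (x, y) in R of b(x; n, p)·b(y; n, p). The common rate 8.5% is the midpoint of 1% and 16%.

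| Setting | Common rate 8.5% | 12% | 16% |
|---|---|---|---|
| 58 per group, one-sided | 2.5% | 2.9% | 3.1% |
| 71 per group, one-sided | 2.9% | 3.1% | 3.1% |
| 71 per group, two-sided | 2.3% | 2.8% | 3.1% |
| 58 per group, two-sided | 1.9% | 2.4% | 2.7% |

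Over all null rates, Fisher's size never exceeds 3.9% in any of the four settings.

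**Step 3: calibrate Boschloo's test.** Order the tables by Fisher P and take the largest cut-off whose maximum size over null rates from 0 to 1 is at most 0.05. The cut-offs on the Fisher P scale run from 0.0625 to 0.0661. The maximum sizes are 4.94% (58 one-sided), 4.94% (71 one-sided), 4.98% (71 two-sided) and 4.67% (58 two-sided). Every cut-off is above 0.05, so every table that Fisher's test rejects is also rejected here.

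An example at 71 per group, two-sided: 0 v 5 intubations gives Fisher P = 2 × (71·70·69·68·67)/(142·141·140·139·138) = 0.058. Fisher's test does not reject. Boschloo's does, because 0.058 is below its cut-off of 0.0642.

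**Step 4: power.** Sum the product of the two binomials over each rejection region.

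| Setting | 1% v 16%: Fisher | Boschloo | Gain | 1.5% v 12%: Fisher | Boschloo | Gain |
|---|---|---|---|---|---|---|
| 58, one-sided | 89.2% | 93.3% | 4.1 | 62.4% | 72.3% | 9.9 |
| 71, one-sided | 95.6% | 97.1% | 1.6 | 75.5% | 81.7% | 6.2 |
| 71, two-sided | 90.4% | 94.2% | 3.8 | 61.5% | 71.7% | 10.2 |
| 58, two-sided | 80.0% | 87.6% | 7.6 | 46.9% | 59.8% | 13.0 |

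Gains are in percentage points, taken before rounding. The plain uncorrected chi-square test is not a substitute: one-sided, its size reaches 6.1% at both group sizes.

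**The case against.** The strongest reply is that nothing here is wrong. Fisher's test is prespecified, standard and exact, and it holds the error rate below 5%. At the planning rates its power is close to target or above it in three of the four settings: 89.2% at 58 one-sided, 90.4% at 71 two-sided and 95.6% at 71 one-sided. The gains of about 10 points need rates on which the trial was not sized. The trial is also open-label and already recruiting (Blinding; Trial status), so a change of primary test needs a documented amendment. All of this stands, and it limits the point to a matter of efficiency.

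Three stronger readings are tempting, and the documents do not support them:

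- **That the stated test cannot deliver the planned power.** In the design's own setting, 58 per group one-sided, the shortfall is 90 − 89.2 = 0.8 points.
- **That the 80.0% at 58 two-sided is the price of Fisher's test.** Of the 10 points below target, 89.2 − 80.0 = 9.2 come from applying a two-sided test to a one-sided sample size. That is a separate matter of stating the sidedness.
- **That the plan is deficient because it names no confidence interval for the effect.** A journal article may leave that to the full protocol or the analysis plan.

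What the reply does not answer is that the protocol itself has fixed the primary test, and that a test with the same 5% guarantee never rejects less often.

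**Conclusion.** The point holds as a minor, optional improvement. At these event rates Fisher's test spends about 2–3% of a nominal 5%. Boschloo's test recovers 1.6 to 7.6 points of power at the planning rates and 6.2 to 13.0 points at the meta-analysis rates, with the same infants and a maximum size at or below 5%. No single gain should be quoted without its group size and sidedness.

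The figures assume that success in the cited study is the complement of intubation, that infants are independent, that the groups are equal in size, and that the true rates are near one of the two pairs the protocol gives. A reader might infer that the trial is underpowered or its error rate compromised because of Fisher's test. Neither follows: the test is valid, and at the planning rates with all 142 infants analysed it has at least 90% power on either sidedness.

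**What to change.** Before data are seen, amend the Statistical analysis section to name Boschloo's unconditional exact test for the primary outcome at 0.05, with the cut-off or P-value maximised over the full range of null rates from 0 to 1. State whether the test is one- or two-sided, and use the same sidedness in the Sample size section. Keep Fisher's test for the other categorical data.

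No extra infants are needed and the 5% limit is kept. The cost is a test that is less familiar to readers and a short amendment. Because the trial is recruiting and unblinded, the amendment should be dated and should record that no outcome data by group had been examined.

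If the sponsor prefers to keep Fisher's test, the alternative is to quote its exact power in the Sample size section for the chosen sidedness, in place of the z-formula figure.
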